### Methodology for irradiation: low level laser specifications and dosimetry

2.5

All participants (G1 and G2) will be irrigated with 20 mL of sterile saline in the gingival sulcus of the lower third molar. Before irradiating 0.4 mL of blue solution, at the concentration of 0.005% will be applicated, which may be conventional MB or a new formula for oral use.^[19]^ As the MB has the function of PS, it will be applied inside the gingival sulcus around the third molar with pericoronitis after 3 minutes, and the irradiation will be initialized.

The red laser diode (Therapy XT DMC, São Carlos, Brazil) (ANVISA 80030810157) with a wavelength of 660 nm (± 10 nm) will be used. The power of the appliance is 100mW. The diameter of the fiber optic device is 600 μm and thus, a spot (area) of 0.002826 cm^2^. It will deliver the energy of 9 J per point in 90 seconds, generating Radiant Exposure (fluence) of 318 J/cm^2^ and irradiance will be 31.8 W/cm^2^. The irradiance will be 3.5W/cm^2^. Participants will receive irradiation at 2 points: 1 buccal and 1 lingual (Fig. 1). During application the volunteer and operator will wear goggles, the active tip of the instrument will be protected with disposable transparent plastic adapted to tip to prevent cross-infection, and the operator will be putting on protective gloves.

**Figure 1 F1:**
[figure not shown]
Irradiation points.

### Outcome measures

2.6

All the variables (except *T forsythia* and cytokines) described below will be evaluated by the same operator at baseline, before PDT (T1), immediately after PDT (T2), and on the 4th day after PDT (T3). *T forsythia,* salivary and crevicular cytokines will be evaluated at T1 and T3.

The primary outcome will be the presence and quantity of bacterium *T forsythia.* Microbiological analysis will be performed by RT-PCR for the bacterium *T forsythia*. Biofilm samples for microbiological analysis, will be collected at 2 points of the vestibular gingival sulcus of the lower third molar using Gracey mifive curettes (Hu-Friedy, Chicago). The collected samples will be maintained in TE (Tris-EDTA), conditioned in microtubes in ice, and later transported to the laboratory analysis in the Microbiology Laboratory of ICB-USP Department of Microbiology, Institute of Biomedical Sciences for laboratory analysis. From these samples, total DNA will be extracted with Step One Plus Thermo-Time PCR System (Applied Biosystem, Foster City, CA) before amplificating them with PCR. The products will be detected by fluorescence using the Quantimix Easy SYG Kit (Biotools, Madrid, Spain), according manufacturer. For the reaction, 10 μL of SYBR Green, 0.5 μL DNA template, 200 mM of each primer corresponding to the gene (described in Table 1) will be used. Amplicons from conventional PCR will be used as quantify control curve.

**Table 1 T1:**

Sequences and reference of the primers.

Secondary outcomes will be pain, swelling, trismus, profile of clevicular cytokines, OHRQoL, and position and classification of the lower third molars.

The pain will be assessed by applying visual analog scale (VAS), consisting of a 100-mm line numbered in centimeters, with 2 closed ends. One end is labeled “0” and the other “100,” meaning no pain and terrible pain, respectively (Fig. 2). Each patient will be instructed to mark a vertical line on the point that best matches the intensity of pain during the evaluation. Instructions on marking will always be given to the patient by the same operator.^[20]^The criteria for the determination of swelling will follow pre-established measurements in the face: corner of the eye to angle of the jaw, tragus to the labial commissure, and tragus to pogonion^[21]^ (Fig. 3). The edema value will be the sum of the 3 pre-established facial measures (using a digital caliper).^[23]^For evaluation of the presence of trismus the inter-incisor will be measured (distance between the incisal edge of the maxillary central incisor and the lower central incisor) will be measured with a digital caliper to determine the buccal opening (Mitutoyo Digimatic Caliper model, Japan).The profile of gingival crevicular fluid (GCF) and salivary cytokines will be evaluated and should be collected before the biofilm collection. It will be assessed by using 10 mL of non-stimulated saliva, kept in ice cubes tubes and sent to the Laboratory of Virology, Institute of Tropical Medicine of São Paulo, University of São Paulo, for further analysis. The GCF will be collected from the mesiobuccal portion of lower third molar in each patient,^[23]^ before PDT (T1) and 4 days post PDT (T3) in both groups. Before collection, the supragingival plaque will be removed using a sterile instrument. The site will be insulated using cotton rolls and dried using a small jet of air (not in the groove/pocket). A sterile paper strip into a microcentrifuge tube will be inserted into the gingival sulcus until resistance. The strip will stay in place for 30 seconds. Strips contaminated with blood will be discarded and the site was resampled after 90 seconds. The GCF strips will be stored in microcentrifuge tubes at −80° C until analysis.^[23]^ The cytokines (interleukin [IL]-1β, IL-6, IL-10, and tumor necrosis factor alpha [TNFα]) from the GCF will be analyzed by high-sensitivity human cytokine 4-plex by Millipore (Millipore Corporation, Billerica, MA). The Milliplex kits were developed with microspheres and were based on immunoassays.OHRQoL will be assessed by Brazilian version of OHIP-14 questionnaire.^[24]^ This instrument consists of 14 items arranged in 7 factors: functional limitation, physical pain, psychological discomfort, physical disability, psychological disability, social disability, and handicap. The answers are given corresponding to a total of 5 points on a Likert-type scale. The scale included the following responses: never (coded 0), hardly ever (coded 1), occasionally (coded 2), fairly often (coded 3), and very often (coded 4). The OHIP-14 scale ranged from 0 to 56, with higher scores indicating poorer QoL.^[25]^ The items of the OHIP-14 are shown in Table 2.Position and classification of the lower third molars will be assessed by panoramic radiography, according to the classification of Pell and Gregory and Winter,^[26]^ performed by only 1 evaluator, following the criteria of imaginary lines as proposed by Almendros-Marques et al.^[27]^

**Figure 2 F2:**

Visual analog scale (VAS).

**Figure 3 F3:**
[figure not shown]
Three pre-established facial measures. The criteria for the determination of edema—(I) corner of the eye to angle of the jaw, (II) tragus to the labial commissure, and (III) tragus to pogonion.

**Table 2 T2:**
[figure not shown]
OHIP-14 questionnaire and its domains.

A flowchart is presented for an overview of the study (Fig. 4).

**Figure 4 F4:**
[figure not shown]
Flowchart presenting an overview of the study.

### Statistical analysis

2.7

The data will be collected, tabulated on Excel table developed for research and presented in a descriptive way. All statistics will be conducted using the SPSS 21 program package (SPSS Inc, Chicago, IL). In the first part of the results will be performed the descriptive analysis. Measures of: absolute number, mean, standard deviation, minimum value and maximum value, percentage and cumulative percentage will be used. The bacterial count will be normalized by conversion into logarithmic values will be compared by the student *t* test. In the second part, we will verify the inferential analysis for the numerical variables. Tests of Normality Skewness and Kurtosis will be used, then verification of the homogeneity of the variables. The ANOVA will be applied for repeated data, and the Spearman correlation, and the Huynh-Feldt, Greenhouse-Geisser, Box's conservative tests. If there is no normality of the sample will be used The Wilcoxon test will be used in order to compare before and after the PDT. The *P* value is set at *P* < .05 (95% level of significance). By the end of the study, randomized groups will be revealed and statistical analysis will be performed as group A or B. The meaning of A or B will be known after statistical analysis. The data will be evaluated by comparing 2 groups: experimental and control groups (gold standard).

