### Sample size calculation

2.1

The sample size was calculated (G∗ Power software version 3.1.9.2, Kiel, Germany) by *t* test for paired groups, since we have 2 groups (G1 conventional PS and G2 oral use PS). The effect size was determined using the formula: 

We select the worst scenario, that is, the largest standard deviation between means. The mean values of control and treated groups, as well as the standard deviation were taken from 1 study.^[18]^ The error was set at 5% and the power test at 95%. This value was calculated to provide 95% strength (α = 0.05). According to the calculus, a ample of 64 patients will be necessary to detect differences in *Tannerella forsythia* level.^[18]^ Other factors related to secondary outcomes will be analyzed statistically.

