### Inclusion and exclusion criteria

2.2

Participants in this study will be evaluated to meet the eligibility criteria: ASA I patients (negative medical history), with age of 13 years old or over till 60 years, with lower third molar erupted or partially erupted, with pericoronitis. Patients should have at least one lower third molar partially visible in the oral cavity to be examined. All participants, regardless of age, gender, cultural level, or socioeconomic status may participate in the study. The following patients will be excluded: those allergic to MB, pregnant or breastfeeding women, with presence of purulent exudate, those who have used anti-inflammatory drugs or antibiotic medications for the last 3 months, those with fever (with temperature above 37.8°C), that may suggest an infection. The local temperature will be measured in the mandibular angle region 2 cm above the lower jaw board (Safety 1st model “No Touch Forehead,” Columbus, OH).

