## Discussion

3

The main rationale for conducting this study is to verify a possibility of treating pericoronitis with a low risk alternative. Other reasons are to suppress or reduce the quantity of antibiotics medications and to test if the new oral formulation with MB is more effective on bacterial reduction.

The primary outcome will be the presence and quantity of bacterium *T forsythia*, and secondary: pain, swelling, trismus, GCF and salivary cytokines, OHRQoL and position and classification of the lower third molars, to avoid bias the measurement of all these outcomes should be standardized.

The bacterium *T forsythia* plays an important role in the development of clinical symptoms of pericoronitis.^[28,29]^ The presence and quantity of *T forsythia* increase in 8 times the risk of developing pericoronitis, when compared to individuals without it.^[28,30,31]^ This bacterium was also associated with the development of pericoronitis in other studies and was present in 40% of their samples.^[32–35]^ Thus, it will be important to measure it properly and quantify this association.^[28]^

PDT causes non-toxic death, leading to destruction of the cell wall and consequent death of the microorganisms. The capacity of PDT to kill bacteria has been studied by several authors; Fontana et al^[16]^ found that bacteria did not reduce to the same degree as has been reported for treatment with antibiotics.

PDT is effective in destroying periodontal pathogens,^[36]^ since most oral bacteria do not absorb the visible light, it is necessary to use the PS, which must act for a period before irradiation.^[37]^

The PS binds to the cell of the microorganism because it needs to bind to negative charges and the membrane of the microorganism has more negative charge than the membrane of the host cell.^[38]^ Gram-negative bacteria induced the dye dimerization more intensely than gram-positive bacteria.^[39]^ The membrane of microorganism are always negatively charged, so the positively charges PS attach and/or aggregate to them and end up interfering on benefits of PDT process.^[40]^

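### The log-and-t-test rule for T forsythia cannot be applied to samples without the bacterium, though the primary outcome counts absence and positivity is not required at entry

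*Protocol article*

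**What the plan says.** All references are to the protocol article.

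- **Outcome (section 2.6).** "The primary outcome will be the presence and quantity of bacterium" T forsythia, measured by PCR at T1 (baseline) and T3 (fourth day after treatment).
- **Analysis (section 2.7).** "The bacterial count will be normalized by conversion into logarithmic values will be compared by the student" t test. Presence has no named test.
- **Fallback (section 2.7).** If normality fails, "The Wilcoxon test will be used in order to compare before and after the PDT". No rank-based comparison between the two arms is named.
- **Eligibility (section 2.2).** Patients enter "with lower third molar erupted or partially erupted, with pericoronitis". A positive T forsythia sample is not required.
- **Detection rate (Discussion).** The bacterium was linked to pericoronitis in other studies "and was present in 40% of their samples". This is the only detection figure in the document.
- **Sample size (section 2.1).** 64 patients, 5% error and 95% power, with means and standard deviation taken from one cited study and not printed.

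**The concern.** The article names both a transform and a test, and the transform is undefined for a category that its own outcome definition creates. Listing presence as part of the outcome concedes that absence will occur. If a large share of samples is negative, the data are a spike at one value plus a spread of positive counts. Taking logs does not turn that mixture into a normal distribution.

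How the negatives are handled can decide the primary result. Statistical software normally returns a missing value for the log of zero. At T3 a missing value would then mean that the bacterium was not found, which is the best possible response. The arm that clears more patients would lose more of its best responders, and the t test would compare only those in whom treatment had not cleared the bacterium. The Discussion says the trial is meant to show whether the new formulation reduces bacteria more, so clearance at T3 is a plausible treatment effect.

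**Working it through.** **1. The plan's own figure.** N = 64 cannot be reproduced, because no means, standard deviation or effect size is printed. I therefore solved backwards for the effect that 32 per arm would detect. Section 2.1 names a paired t test, but the arms are parallel, so I used the independent two-sided t test at 5%. Its noncentrality is d × √(n/2) with 2n − 2 degrees of freedom. For n = 32 and 95% power, d = 0.916 (noncentrality 0.916 × 4 = 3.66).

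**2. Power if only detected samples are analysed.** Two assumptions are made: d = 0.916 applies among carriers, and non-detects drop out. With detection rate p, the number analysed per arm is 32p.

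| Detection rate | n per arm | Noncentrality | Power |
|---|---|---|---|
| 30% | 9.6 | 2.01 | 47% |
| 40% | 12.8 | 2.32 | 60% |
| 50% | 16.0 | 2.59 | 71% |
| 60% | 19.2 | 2.84 | 79% |
| 80% | 25.6 | 3.28 | 89% |
| 100% | 32.0 | 3.66 | 95% |

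At 40%, about 19 of 32 patients per arm (32 − 12.8 = 19.2) would have no log value at baseline.

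**3. Does dropping zeros hide a benefit?** This is a separate question from the smaller n. Suppose carriers are cleared in 20% of the conventional arm and 50% of the new-formulation arm, with equal counts in those not cleared. A t test on the remaining logs rejects in 5% of simulated trials, which is the error rate under no difference. The benefit is invisible.

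A second check used full carriage, d = 0.916, and a conventional-arm mean 1 SD above the detection limit. Power was 92% when values below the limit were set to the limit, and 50% when they were dropped.

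**4. Which handling recovers information?** Simulation assumptions: 40% carriers, baseline log10 mean 5 and SD 1, baseline-to-T3 correlation 0.5, a 2-log fall in the conventional arm and a further 0.92-log fall in the other.

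| Analysis at T3 | Power |
|---|---|
| Zeros dropped, t test | about 57% |
| log10(count + 1), t test | about 16% |
| Change in log10(count + 1), t test | about 17% |
| log10(count + 1), all patients, baseline log count as covariate | about 71% |

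Under other assumptions (40% carriage, conventional-arm carriers averaging 1 to 3 SD above the limit at T3), dropping non-detects gave 20% to 57% power. Setting them to the limit without baseline adjustment gave 15% to 36%. Substituting a value is therefore no cure by itself. In the table above, the gain comes from the baseline sample, which separates non-carriers from carriers.

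**The case against.** **The 40% is not a planning value.** It is a remark about other studies. The article does not say whether samples there means patients or sites, or what the detection limit was. A reader might infer that the trial expects 40% carriage, but the document does not say so, and detection here could be higher. This objection stands, and it is why the result is given over a range.

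**The stated power is not shown to be lost.** A reader might infer that the 95% presumes every patient carries the bacterium. Nothing printed supports that. Section 2.1 says the largest standard deviation was chosen, and it may already include non-detects. The effect of 0.916 is back-solved from an independent test while the article names a paired one. This also stands: the percentages are conditional.

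**Dropping zeros is not stated.** Correct. Log conversion of PCR counts can include an offset or a detection-limit value, and an article may leave that detail to a fuller document. What remains is that the rule as printed cannot be carried out on non-detects, that the between-arm comparison has no stated fallback, and that half of the primary outcome has no test. The planned percentages can describe presence but do not compare it.

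**The 57% is not evidence of lost responders.** In that simulation hardly any carriers reach zero, so the loss reflects the smaller number analysed. The hidden-benefit effect rests on the separate checks in step 3.

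**Multiplicity.** A reader might infer that two primary outcomes inflate the false-positive rate. Only quantity has a named test, section 2.1 powers on the level of the bacterium, and the two measures come from one assay and are dependent. No inflation figure is supported. The role of presence still needs stating.

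**Conclusion.** The concern holds in a bounded form. The primary analysis as written is undefined for samples without T forsythia, the trial admits such patients, and the one cited detection rate suggests they could be numerous. If non-detects are treated as missing, the analysis selects on the outcome and can conceal a true difference in clearance.

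The size depends on two assumptions that the document neither makes nor excludes: that 32 per arm gives 95% power at d of about 0.92 among carriers, and that only detected samples are analysed. Power is then about 60% at 40% detection and 89% at 80%. It cannot be concluded that the trial expects 40% carriage or that its stated power is wrong. The handling of non-detects must be fixed before the data are analysed, because the choice can change the primary result.

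**What to change.** 1. **One primary variable in section 2.7.** Use the T3 log10 count, with a stated detection limit and a stated value for non-detects (for example half that limit). Keep all randomized patients, and compare arms with the baseline log count as covariate. The data will still not be normal, so add a left-censored (Tobit) model as sensitivity analysis.
2. **Presence as a secondary outcome.** Compare detection at T3 between arms by Fisher's exact test or logistic regression.
3. **Supporting analysis.** Repeat the primary comparison in patients positive at baseline, a subset fixed before treatment.
4. **Section 2.1.** State the detection rate assumed behind N = 64 and give the power over a range of rates.

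The cost is analysis wording and possibly a less favourable power statement. The baseline sample is already planned, so no new samples are needed. Keeping 32 detected patients per arm at 40% detection would be a different decision: 32 / 0.40 = 80 per arm, 160 in total.

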**Method::**

In this randomized, controlled, double-blind clinical bioequivalence protocol, 64 healthy patients with pericoronitis will be evaluated. Patients will be randomized into the positive control group (G1) (n = 32): irrigation with sterile saline and PDT (conventional MB at 0.005% concentration and irradiation with low intensity laser λ = 660 nm, 9J per point and radiant exposure of 318 J/cm^2^), and the experimental group (G2) (n = 32): treatment identical to G1, however, MB will be delivered in a new formulation for oral use. Microbiological analysis will be performed by RT-PCR for the bacterium *Tannerella forsythia.* Gingival crevicular fluid and saliva will be collected to evaluate cytokines by Luminex assay (Luminex Corporation, Austin, TX). The pain (visual analogue scale), swelling and buccal opening (digital caliper), and OHRQoL will also be evaluated through the OHIP-14 questionnaire. The variables will be evaluated in T1 (baseline), T2 (immediately after PDT), and T3 (4th day after PDT). Registration: clinicaltrials.gov NCT 03576105. Registered in July 2018.

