### Randomization

2.3

An external researcher who will not participate in this study will perform randomization through the Microsoft Excel program, version 2013 (Microsof, Redmont, WA). To decide the type of the PS, another researcher will randomize into 4 blocks with 16 patients blocking in pairs of numbers (1:1) designed as A or B. As the study will be performed in a double-blind manner, neither the patient nor the operator will know which MB will be used as PS. To randomly distribute the treatments, the same researcher (not involved in the study) will prepare the envelopes. The letters (A or B) drawn will be placed into opaque envelopes labeled with sequential numbers. The envelopes will be sealed and remain in the same numerical order in a safe place until PDT treatment. These data will only be revealed after statistical analysis.

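### The primary bacterial count is compared by a t test with no baseline covariate and no stated contrast, although it is measured at T1 and T3; ANCOVA on T1 would be more precise

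*Protocol article*

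**What the plan says.** Section 2.6 of the protocol article makes the presence and quantity of *T forsythia* the primary outcome. It schedules that count, along with the cytokines, at baseline and day 4: "salivary and crevicular cytokines will be evaluated at T1 and T3". Pain, swelling, mouth opening and OHIP-14 are measured at T1, T2 and T3.

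Section 2.7 gives the primary method: "The bacterial count will be normalized by conversion into logarithmic values will be compared by the student" t test. No time point, change score or covariate is attached to it. For the numerical variables the section adds "The ANOVA will be applied for repeated data", with a Wilcoxon before-versus-after comparison if normality fails. It closes by saying that the experimental and control groups will be compared. No outcome has a baseline covariate.

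Allocation (section 2.3) is by "blocking in pairs of numbers (1:1) designed as A or B". The baseline count is not a stratification factor. Each arm has 32 patients.

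**The concern.** Both arms receive the same irrigation and laser treatment and differ only in the methylene blue formulation, so the between-arm contrast is the whole question and 64 patients have to answer it. The design already collects a baseline count, and baseline is usually the most useful covariate for the same measurement four days later. A Student t test has no place for it as a covariate. Either the test uses T3 alone and leaves the baseline out, or it uses the change and forces the slope on baseline to be exactly 1. In both cases the confidence interval is wider than it need be, and a chance difference at T1 carries over in part into the estimated treatment effect. Randomisation that is not stratified on the T1 count does nothing in the design to limit that difference.

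**Working it through.** **Inputs.** From the document: 32 per arm (Abstract and section 2.4); α and power from section 2.1, "The error was set at 5% and the power test at 95"%; count at T1 and T3 (section 2.6). Assumptions: two-sided test, no dropout, equal SD at T1 and T3, a linear relation between the log counts, and a T1–T3 correlation r. The document gives no r, so a range is shown.

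**The plan's own figure.** Section 2.1 concludes that "a ample of 64 patients will be necessary to detect differences in" the *T forsythia* level. The text gives no means, SD or effect size ("The mean values of control and treated groups, as well as the standard deviation were taken from 1 study"), so 64 cannot be rebuilt forward. Working backwards with the noncentral t distribution, an independent-groups comparison with 32 per arm has 95% power for a difference of 0.916 SD. That is used below only as a reference point.

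**Variance of the between-arm difference, relative to a t test on T3 alone.**
- T3 alone: 1
- Change from T1: 2(1 − r)
- ANCOVA of T3 on arm and T1: 1 − r²

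Relative to the change score, the ANCOVA variance is (1 − r²) / [2(1 − r)] = (1 + r)/2. For any r strictly between 0 and 1 it is therefore below both t tests.

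**Power at a true difference of 0.5 SD.** The noncentrality is 0.5 × √(32/2) / √(variance ratio) = 2.0 / √(variance ratio), with 62 degrees of freedom for the t tests and 61 for ANCOVA.

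| r (assumed) | Variance ratio, change | Variance ratio, ANCOVA | Power, T3 alone | Power, change | Power, ANCOVA |
|---|---|---|---|---|---|
| 0.2 | 1.60 | 0.96 | 50% | 34% | 52% |
| 0.3 | 1.40 | 0.91 | 50% | 38% | 54% |
| 0.5 | 1.00 | 0.75 | 50% | 50% | 62% |
| 0.7 | 0.60 | 0.51 | 50% | 72% | 79% |

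**Detectable difference at 95% power.** This is 0.916 × √(1 − r²), which gives 0.87, 0.79 and 0.65 SD at r = 0.3, 0.5 and 0.7, against 0.916 SD for T3 alone.

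**Patients per arm for 95% power at 0.916 SD.** T3 alone needs 32. ANCOVA needs 31, 30, 25 and 17 at r = 0.2, 0.3, 0.5 and 0.7. At r = 0 it needs 33, because one degree of freedom is spent for nothing.

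**Chance imbalance.** The difference in T1 means between arms has a standard error of √(2/32) = 0.25 SD. An imbalance of that size shifts the T3-only estimate by r × 0.25 SD, which is 0.075, 0.125 and 0.175 SD at r = 0.3, 0.5 and 0.7. It shifts the change-score estimate by (r − 1) × 0.25 SD, which is −0.175, −0.125 and −0.075 SD. ANCOVA removes the shift under the linear model.

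**Do the other planned tests make up for this?** For an outcome with two time points, the group-by-time term of a repeated-measures ANOVA is the same test as a t test on the change, so it is already in the table. The Wilcoxon fallback compares before with after and is not a baseline-adjusted comparison of arms.

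**The case against.** The best counter-argument is that the text does not say the t test ignores T1. A reader might infer that it does, but section 2.7 fixes neither T3 nor change. Other wording leans towards using baseline: the sizing in section 2.1 is by a paired t test, and the Discussion speaks of bacterial reduction. If the change is tested, T1 is used, and at r = 0.7 the gain from ANCOVA is from 72% to 79%, not from 50% to 79%. This stands, and it is why both readings are shown. It does not remove the point, because ANCOVA has the smaller variance under each. A within-arm before-and-after t test would not compare the arms at all, and section 2.7 says that the groups will be compared.

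Two further readings are tempting and unsupported. One is that the repeated-measures ANOVA will be judged on its group main effect, which would average in a time before treatment. Section 2.7 does not say which term is read. The other is that swelling, a sum of three facial distances, will mainly reflect face size. That falls away if the group-by-time term is used, since stable face size then cancels within patient.

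It is also fair to say that the unadjusted test keeps its type I error under randomisation, and that its standard error already allows for chance imbalance on average. So nothing here makes the planned test invalid. Covariate choice can be left to an analysis plan, but this article does name a method for its primary outcome, and a better one is available from data already being collected.

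Finally, the Discussion cites other studies in which the bacterium was present in 40% of samples. Many counts may be non-detects, where a logarithm is undefined and a linear model is less comfortable. That is a real limit on any gain. The planned t test on log counts faces the same problem.

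**Conclusion.** The point holds as one of efficiency and conditional bias. The primary contrast is left open between T3 and change, and no baseline covariate is named. Under either between-arm reading ANCOVA gives a tighter estimate and takes out chance T1 imbalance. The size depends on a correlation that the document does not give. Against T3 alone the gain is slight at r = 0.3 or below (4 percentage points of power at 0.5 SD, or 30–31 against 32 patients per arm) and substantial at 0.5 and above (12 to 29 points). Against change, it is 16, 12 and 7 points at r = 0.3, 0.5 and 0.7. These figures assume equal SDs, linearity, complete data and few non-detects. The change is worth making before unblinding, but the trial's validity does not depend on it.

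**What to change.** State in section 2.7 that the primary between-arm test is an ANCOVA of log10 *T forsythia* at T3 on treatment arm, with log10 T1 as covariate, and report the adjusted G2–G1 difference with its 95% CI. Fix in advance one value to be used for non-detects at T1 and T3.

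Use the same model, T3 on arm and T1, for the continuous secondary outcomes: pain, swelling, mouth opening, cytokines and OHIP-14. It does not apply to third-molar position and classification, which is categorical. Where repeated measures are kept for outcomes with a T2 value, model the post-treatment values with T1 as covariate and read the arm effect at T3.

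The cost is a few sentences in the plan, one degree of freedom and slightly more analysis work. No new data are needed.

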## Methods

2

The protocol was approved by the Research Ethics Committee of Nove de Julho University (UNINOVE), number # 2.732.106 and registered at clinicaltrials.gov NCT 03576105. The study is in accordance with the Declaration of Helsinki (revised in Fortaleza, 2013).

Participants who accept to participate will sign the Informed written Consent Form after verbal and written explanation of the study. The sample will comprise 64 healthy patients of both genders aged from 13 to 60 with pericoronitis. After agreeing to participate, in a bio-equivalence study, participants will be evaluated in 3 different moments: baseline before PDT (T1), immediately after PDT (T2), and 4th day after PDT (T3). The clinical evaluation and the PDT treatment will be performed by the same researcher, in all 3 moments at the Dental Clinic at Nove de Julho University—UNINOVE, São Paulo, Brazil, from March, 2019 until September 2019.

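### The named repeated-measures ANOVA would, unless missing values are filled in first, drop every patient without a day-4 value; a mixed model on all observed visits is better and costs almost nothing

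*Protocol article*

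**What the plan says.** The Statistical analysis section (2.7) of the protocol article fixes the software ("All statistics will be conducted using the SPSS 21 program package") and announces a second part in which "we will verify the inferential analysis for the numerical variables". After checks of normality and homogeneity, "The ANOVA will be applied for repeated data", together with the "Huynh-Feldt, Greenhouse-Geisser, Box's conservative tests". Those corrections belong to the univariate repeated-measures ANOVA. For non-normal data the fallback is: "The Wilcoxon test will be used in order to compare before and after the PDT". The section closes by saying that the experimental and control groups will be compared.

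The section does not list the numerical variables. Outcome measures (2.6) schedules everything except *T forsythia* and the cytokines at three time points: baseline, directly after treatment, and day 4. The numerical outcomes on that schedule are pain (VAS), swelling, mouth opening and OHIP-14, all secondary. The primary outcome, the *T forsythia* count, is compared by t test and is not part of this point.

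The article states no expected dropout, analysis set, imputation or mixed model.

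**The concern.** T1 and T2 lie on either side of the same treatment. T3 is a separate visit on day 4. The natural pattern of missing data is therefore a patient with T1 and T2 recorded and T3 absent. SPSS repeated-measures ANOVA takes one row per patient and omits a row with any visit missing, so that patient's two recorded values are not used.

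Two things are at stake. The first is precision: comparisons at T1 and T2, where values exist for everyone, would be made on returners only. The second is the arm comparison at T3. If return depends on how the patient felt earlier, and the arms differ in that respect, the returners in the two arms are no longer comparable in the way randomisation made them.

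**Working it through.** **No figure of the plan to reproduce.** The article gives no dropout rate and no SD for these outcomes. All inputs below other than the arm size are assumptions.

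**1. Data lost.** With 32 per arm, rounding completers per arm to whole patients, each non-returner loses two recorded values per outcome:

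| Assumed loss | Completers of 64 | Recorded T1/T2 values unused per outcome |
|---|---|---|
| 5% | 60 | 2 × 4 = 8 |
| 10% | 58 | 2 × 6 = 12 |
| 15% | 54 | 2 × 10 = 20 |
| 20% | 52 | 2 × 12 = 24 |

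At 20% loss, the standard error of a T2 comparison is inflated by √(64/52) = 1.11.

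**2. Possible bias in pain at T3.** Assumed inputs:
- SD 20 mm at each visit; T2–T3 correlation 0.7.
- Control mean 40 mm at T2; experimental mean lower by 5, 10 or 15 mm.
- True T3 difference 10 mm.
- Half of patients with T2 below 20 mm do not return, by the same rule in both arms.

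For an arm with T2 mean μ, put c = (20 − μ)/20. Non-return is 0.5·Φ(c). Among returners the T2 mean is raised by 0.5 × 20 × φ(c) / (1 − 0.5·Φ(c)), and the T3 mean is raised by 0.7 times that amount.

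| Arm | μ | c | Non-return | Rise in T2 mean (mm) | T3 difference in completers (mm) |
|---|---|---|---|---|---|
| Control | 40 | −1.00 | 7.9% | 10 × 0.2420/0.9207 = 2.63 | – |
| Experimental, T2 difference 5 | 35 | −0.75 | 11.3% | 10 × 0.3011/0.8867 = 3.40 | 10 − 0.7 × 0.77 = 9.46 |
| Experimental, T2 difference 10 | 30 | −0.50 | 15.4% | 10 × 0.3521/0.8457 = 4.16 | 10 − 0.7 × 1.53 = 8.93 |
| Experimental, T2 difference 15 | 25 | −0.25 | 20.1% | 10 × 0.3867/0.7993 = 4.84 | 10 − 0.7 × 2.21 = 8.45 |

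A simulation with 400,000 patients per arm (other correlations 0.7 and 0.6) agrees: 9.51, 8.98 and 8.45 mm in completers. Regressing T3 on T1 and T2 within arm, which uses the non-returners' values under missing-at-random, gave 10.05, 10.01 and 10.01 mm.

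**3. When there is no bias.** If both arms have the same T2 mean, both rises are equal and cancel, so completers give 10 mm. If non-return is unrelated to T2, there is likewise no bias.

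**4. A deliberately adverse case.** In 2,000 simulated trials of 32 per arm, with no true T3 difference and equal correlations of 0.3 to 0.7, return was made to depend on T2 in opposite directions in the two arms. The shift in completers was 0.05–0.09 SD at 5% loss, 0.08–0.17 SD at 10% and 0.14–0.32 SD at 20%. With T1 and T2 kept it was at most 0.012 SD. With the same rule in both arms it was about 0. The spread of the T3 estimate was nearly the same for both methods (for example 0.274 against 0.281 SD at 20% loss and correlation 0.5), so keeping T1 and T2 guards against bias at T3 but adds little precision there.

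**5. When the remedy is incomplete.** If non-return depends on T3 pain itself, completers give 8.5 to 8.6 mm and the missing-at-random analysis about 9.3 mm. The error falls from about 1.5 to about 0.7 mm, roughly half.

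**The case against.** The strongest objection is that the article never says incomplete patients are excluded. A full protocol or SAP may hold a missing-data rule, and imputation before the ANOVA would be compatible with section 2.7. That stands. A reader might infer that the plan as written deletes all non-returners; the documents support this only on condition that nothing is filled in first. What remains is that the article does commit to a method and a package, and that the method by itself cannot use an incomplete patient.

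The size is also open to challenge. With SD 20 mm and 32 per arm, the standard error of the arm difference is 20 × √(2/32) = 5.0 mm, so a bias of 0.5 to 1.5 mm is 0.1 to 0.3 of one standard error. It requires an arm difference directly after treatment, although both arms receive the same irrigation, dye concentration and laser, and patient and operator are blinded. Follow-up is a single visit four days later. All of this stands and limits the weight of the point.

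Two further inferences are tempting. One is that 64 patients leave no room for loss on these outcomes. The Sample size calculation section says "64 patients will be necessary to detect differences in" *T forsythia* level, the primary outcome. No power is claimed for the secondary outcomes, so the figure says nothing about their margin. The other is that all four outcomes are biased. Only pain was examined numerically, and bias in any outcome depends on how it relates to the reason for not returning.

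**Conclusion.** The point holds as a modest improvement to a stated method for secondary outcomes. Repeated-measures ANOVA in SPSS, with nothing filled in, drops patients without T3 along with their T1 and T2 values. The bias is conditional: about 0.5 to 1.5 mm out of 10 mm on the VAS under the inputs assumed above, towards no difference. It is nil if return depends on T2 in the same way in both arms and the arms are equal at T2. If all patients return, nothing is lost at all. The actual dropout is unknown, and the link to the four outcomes is inferred from the wording on numerical variables and the visit schedule. The primary comparison is untouched. The case for changing rests on the low cost of a method that never uses less of the data, not on a demonstrated bias.

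**What to change.** In section 2.7, replace the repeated-measures ANOVA with a linear mixed model (SPSS MIXED), and name the outcomes to which it applies. Fixed effects are arm, time and arm-by-time, with unstructured covariance across T1, T2 and T3. Include every available value of all randomised patients in their allocated arm. Report the arm contrast at T3 with its 95% CI. The Huynh-Feldt, Greenhouse-Geisser and Box corrections are then not needed. Report the number of missing T3 values and the reasons, by arm.

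The cost is a change of wording: same software, same data, no extra patients or visits. The downside is that the model relies on missing-at-random and only partly corrects the contrast when non-return depends on day-4 symptoms that nobody recorded. A simple sensitivity analysis should therefore go with it, for example varying the assumed T3 values of non-returners separately by arm over a stated range.
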